### Sample size determination

We calculated the sample size for our study using Bonferroni correction to adjust for two primary outcome measures: weight and HbA1c. With an overall alpha level of 0.05, the adjusted significance level for each outcome was set to 0.025. Assuming a power of 95%, the required sample sizes were determined based on Cohen’s d effect sizes of 0.445 for weight and 0.635 for HbA1c, based on a previous study by Lean et al. (2018) [18]. The calculations indicated a sample size of 132 participants per group for weight and 65 participants per group for HbA1c level. To ensure adequate power for both outcomes, we selected the larger sample size requirement, resulting in a total sample size of 132 participants per group. To account for the potential dropout and loss to follow-up of 30%, the final sample size was estimated at 360 (180 in each group).

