### Statistical analyses

Primary outcome measures will be analysed using two-sided statistical tests with a type I error rate of α = 0.05. Primary analysis will be performed using the intention-to-treat method. Categorical data will be compared between the two groups using chi-square or Fisher’s exact tests. Continuous data will be evaluated using parametric or non-parametric tests based on data distribution.

For outliers (± 3 standard deviation), efforts will be made to cross-check and obtain the correct values. Failing this, the case will be considered as missing data. In the case of random missing values, two separate analyses will be performed: one including the cases with missing data by choosing pairwise deletion and the other excluding it using listwise or case-wise deletion. A complete case analysis will be considered if differences are observed between the two analyses. In the case of non-random missing values, the imputation method may be used by replacing the missing value with the mean for that variable.

Potential adjustments for baseline values, age, gender, and disease duration may be considered. Multivariable linear and logistic regression analyses will be used to determine predictors of remission. Finally, subgroup analyses may be performed based on factors such as gender, age, comorbidity, diagnosis length, and severity to investigate potential variations in treatment responses.

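### Mean replacement is the only method named for non-random missing values; it is the wrong value there and unusable for the two binary primary outcomes, with 30% loss expected

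*Protocol article*

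**What the plan says.** The Statistical analyses section states the principle first: "Primary analysis will be performed using the intention-to-treat method". It then treats missing values in two branches.

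- **Random missingness.** Two analyses are run, "one including the cases with missing data by choosing pairwise deletion and the other excluding it using listwise or case-wise deletion". On what follows, the text says: "A complete case analysis will be considered if differences are observed between the two analyses".
- **Non-random missingness.** Here "the imputation method may be used by replacing the missing value with the mean for that variable". No other method is named for this branch, and the text does not say whether the mean is that of the participant's own group or of everyone.

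The same section sends outliers beyond 3 standard deviations that cannot be corrected into the missing pool: "Failing this, the case will be considered as missing data". The Sample size determination section gives the expected scale: "To account for the potential dropout and loss to follow-up of 30%, the final sample size was estimated at 360 (180 in each group".

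The Outcome measures section defines both primary outcomes as yes/no: weight loss of at least 10%, and remission. The Statistical analyses section compares categorical data by chi-square or Fisher's exact test.

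**The concern.** Missingness is non-random when the unseen values differ systematically from the seen ones. The observed mean is then the one value known not to represent the people who were lost. So the plan offers mean replacement in the situation that it suits least.

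Outcome-related loss is plausible in this trial, although the documents do not quantify it. The trial is open-label and non-randomised, the intervention is a paid subscription, weight is self-reported, and failure to comply is listed as a ground for discontinuation.

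Three things are at stake: whether the rule can be applied to the primary outcomes at all, whether standard errors of continuous weight and HbA1c would be honest, and whether the estimated effect would be distorted.

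**Working it through.** **1. The plan's own scale.** 30% of 180 is 54 lost per group, leaving 126 observed. The stated 180 is not exactly 132 inflated for 30% loss (132/0.7 = 188.6; 132 × 1.3 = 171.6). Falling from 180 to 132 is a 26.7% loss. That mismatch is a separate matter; here only 180 and a loss of 27% to 30% are needed.

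**2. Binary primaries.** If 30% of those observed were in remission (an assumed rate), the mean of the 0/1 variable would be 0.30. A participant cannot be entered in a 2 × 2 table as 0.30 of a remission. Filling HbA1c or percentage weight loss first and applying the cut-off afterwards does not help: everyone given the same filled value falls on the same side of it. Up to 54 of 180 in an arm, or 30 percentage points, would then meet or miss that threshold together.

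**3. Continuous outcome, arm mean.** Let n be the number analysed per arm and m the number observed. Filled values add nothing to the sum of squares, yet they are counted in the sample size.

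- Reported SE = s·√((m−1)/(n−1))·√(2/n). True SE = s·√(2/m).
- Ratio = √[((m−1)/(n−1))·(m/n)].
- At n = 180, m = 126: √[(125/179)(126/180)] = 0.699.
- Actual error of a nominal 5% test = 2·(1 − Φ(1.96 × 0.699)) = 17.1%. A nominal 95% interval covers 82.9%.

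| Share imputed | SE ratio | Actual error at nominal 5% |
|---|---|---|
| 20% | 0.80 | 11.7% |
| 26.7% | 0.73 | 15.1% |
| 30% | 0.70 | 17.1% |
| 40% | 0.60 | 24.0% |

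At 30% imputed and the 0.025 level used in the sample size section, the error is 11.7%. A simulation of 10,000 runs with loss unrelated to outcome gave 16.9% at nominal 5%, and 5.0% for complete cases.

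**4. Continuous outcome, overall mean.** With a fraction f lost in each arm, unrelated to outcome, the difference between arms becomes (1 − f)·d = 0.7 × 0.445 = 0.31. The simulation gave 0.312, with type I error of 4.9%. Power was almost unchanged (94.0% against 94.1% for complete cases), so the damage is to the estimate and its interval.

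**5. Loss that depends on outcome (assumed mechanism).** The odds of loss were set to match 30% at the arm average, with log-odds rising by 1 per SD of worse outcome. The true effect was zero.

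| Where loss depends on outcome | Arm mean: estimate, error | Overall mean: estimate, error |
|---|---|---|
| Intervention arm only | +0.28 SD, 82% | +0.19 SD, 62% |
| Both arms alike | 0.00 SD, 19% | 0.00 SD, 4.9% |

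Neither mean corrects loss that differs between arms. With a true d of 0.445 and outcome-dependent loss in the intervention arm only, the overall mean gave 0.49, so it does not always dilute.

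**The case against.** The other side has several good points.

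- **The wording is permissive.** Mean replacement may be used, and complete cases will be considered. This stands: the defect is an unsound option, not a fixed rule. Still, it is the only option named for non-random loss.
- **The 17% needs a reading that the text does not state.** The rule speaks of the variable's mean without mentioning group, and the overall mean is arguably the plainer reading. The figure also assumes that all the loss is imputed and the outcome is continuous. If half of the 30% were random and deleted, 27 of 153 per arm would be imputed. The ratio would then be √[(125/152)(126/153)] = 0.823 and the error about 10.7%. This stands, so 17% is conditional and is not the error rate of the primary tests.
- **The complete-case fallback.** A reader might infer that it biases the result too. The documents do not support that. The fallback belongs to random missingness only, and under random loss complete cases were unbiased in simulation (0.446 for a true 0.445, error 5.0%). Examples in which it misleads, such as assumed remission of 30% against 5% reading as 42.9% against 7.1% when every lost participant is a failure, assume non-random loss, which the plan sends to the other rule. For a two-group test of one outcome, pairwise and listwise deletion also use the same people unless listwise deletion spans other variables.
- **Intention-to-treat.** A reader might infer that nothing in the passage respects it. That goes too far: imputation keeps everyone in their enrolled group, and its fault is the value filled in. The objection fits deletion only, which drops enrolled participants despite the stated primary analysis.

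None of this makes the observed mean suitable for non-random loss or usable for a yes/no primary outcome.

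**Conclusion.** The point holds in this limited form. The only method named for non-random missing values is unsuitable for them, leaves open which mean is meant, and gives no usable value for either binary primary outcome. That conclusion needs no assumed dropout pattern.

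The sizes are conditional. For continuous weight or HbA1c with all 30% imputed and loss unrelated to outcome, the arm mean reports about 0.70 of the true standard error (about 17% error at nominal 5%; about 12% if 20% is imputed), and the overall mean turns 0.445 into about 0.31. The bias under outcome-dependent loss rests on an assumed mechanism and is illustrative only.

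For the random branch the finding is narrower: deletion sits badly with the stated intention-to-treat analysis, but bias is not shown there.

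**What to change.** Delete mean imputation and replace it, before outcomes are analysed, as follows.

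- **Remission and weight loss of at least 10%:** keep all enrolled participants in their group and count a missing outcome as not achieved in the primary analysis. Give multiple imputation by group as a sensitivity analysis. Counting missing as not achieved is one defensible convention among several and penalises the arm with more loss, so the sensitivity analysis should be reported beside it.
- **Continuous weight and HbA1c:** use multiple imputation by group, or a mixed model with baseline and the other visits.
- **Non-random loss:** add a delta-adjusted sensitivity analysis that makes the values of lost participants progressively worse and shows when the conclusion changes.

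If pairwise and listwise deletion are kept, label them as supportive so that they do not displace the intention-to-treat analysis.

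The cost is a change of wording, a little more analysis work and wider intervals. No further participants or data are needed.

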### Trial status

The recruitment process commenced on 1 March 2024 and is expected to finish by 31 August 2024.

## Discussion

Current diabetes management practices typically involve the use of medications to control blood sugar, lipids, and blood pressure [28]. However, these pharmacological interventions do not necessarily address the long-term complications associated with type 2 diabetes (T2D), particularly in cases of non-compliance with treatment or ineffective treatment regimens [29]. A more comprehensive approach to diabetes management, including dietary modification, regular physical activity, and psychological support, may help prevent long-term complications and slow disease progression.

Our study, which spans a period of one year, seeks to effectively manage and achieve remission of T2D through the implementation of dietary interventions, exercise regimens, psychological therapies, and medical management. The DiRemI study represents the first trial in India aimed at T2D remission using an online delivery mode, with a focus on regional, biological, cultural, and lifestyle differences between the study participants. The innovative aspect of our study is the integration of a personalised, holistic, and sustainable healthcare regime that draws on the traditional aspects of the Indian way of life to enhance adherence to treatment protocols. Our study will compare the outcomes of personalised holistic interventions, including diet, exercise, psychological therapies, and medical management, with those of a control group receiving routine medical care.

Several studies have demonstrated the effectiveness of low or very low carbohydrate, low fat, intermittent energy restriction, total diet replacement, and Mediterranean diet for weight loss in participants with T2D [18, 30–36]. However, our dietary intervention program differs from these studies in that it focuses on modifying existing diets by adjusting calorie intake to align with an individual’s health needs, preferences, and dietary norms. This approach ensures that positive dietary changes are sustainable beyond the program’s immediate timeframe and extend into the post-intervention period. In our trial, in conjunction with dietary modifications, individuals will receive tailored guidance to enhance stability, flexibility, and endurance across a range of physical activities and yoga, based on their age, body weight, and fitness levels, as part of the sustainable remission objective.

The importance of mental health is unparalleled and closely connected to effective T2D management. In addition to dietary and exercise adjustments, this trial encompasses a multifaceted approach to both physical and mental well-being, which has not been extensively addressed in previous studies. Research has demonstrated that participants with T2D who experience depression are twice as likely to exhibit non-adherence to medications for diabetes, blood pressure, and cholesterol when compared to non-depressed participants [37]. Moreover, individuals with poorer diabetes self-care tendencies generally exhibit heightened levels of psychological distress, diminished social support, and decreased self-efficacy [38]. In the proposed trial, T2D participants will receive psychological support from trained psychologists to help address and cope with life stressors and achieve optimal disease management.

Another unique feature of our study is the focus on medical management. Unlike previous studies on ILI [17, 39] that completely withdrew all diabetes medicines before the commencement of the trials, in our study, the physician will ensure systematic tapering of medications based on daily reported blood sugar levels. This approach will ensure appropriate medical management of participants with a longer duration of diabetes and, hence, more complications. Furthermore, medical management will address and correct nutritional deficiencies through supplementation.

Our study differs from many other studies on ILI, which have generally focused on specific population demographics (e.g. younger age and newly diagnosed T2D) [35, 39, 40] and limited interventions targeting specific features, such as low/very low-calorie diets, diet replacement, and weight loss, with less emphasis on physical activity and intensive exercise training [36, 41]. Our study represents a unique approach that incorporates a comprehensive, personalised methodology specifically designed to accommodate the distinct features of each participant, with a particular focus on a demographically varied group of individuals aged between 30 and 70 years, who have been living with diabetes for up to 15 years.

In this context, this study aims to contribute to the growing body of evidence supporting the effectiveness of holistic interventions in managing T2D, particularly in diverse populations, such as those in India. By addressing not only physical health, but also mental well-being and cultural considerations, our findings may pave the way for more tailored and effective diabetes management strategies globally.

Our study has a few limitations that should be considered. First, the socioeconomic status of the participants may limit the generalisability of our findings to the broader Indian context because our online diabetes management program operates on a subscription-based model that may restrict access to those who can afford it. Future trials adopting a randomised-controlled design may be planned based on the outcome of the present study to address this. Second, the study relies on self-reported parameters, such as anthropometry, which may be subject to data errors despite detailed instructions and regular monitoring of incoming data. Additionally, although our study is not a true randomised controlled trial, we have chosen a matched-control group for our intervention group which is more acceptable in a real-world setting. Finally, due to the comprehensive nature of our planned intervention, we will not be able to examine the impact of individual components. Notwithstanding these limitations, we believe that our research will provide valuable insights into the effectiveness of our holistic diabetes management program.

## Conclusion

Our protocol of diabetes management proposes an alteration from a medical treatment-focused approach to a comprehensive lifestyle strategy that incorporates physical activity, psychological support, medical management, and dietary modifications. A crucial aspect of our holistic approach is to make the intervention more practical, customised, and adaptable for participants.
